#### Deviations from planned design and consequences for analysis

As mentioned earlier, one deviation from the research design was that the randomized assignment to Batches 1 and 3 was not adhered to. This happened in our case for 20 out of 310 villages. Because this misallocation occurred in relatively few villages, these can be accommodated by using an instrumental variable (IV) estimator in (3). In this case, *T*_*j*_ in (3) is replaced with the actual batch, or the time period of the actual intervention at the time of the survey, and is instrumented with *T*_*j*_. A comparison between the non-instrumented estimate and the IV estimate is insightful in this case. To estimate the impact of the entire project at endline using (1), there is only the non-experimental estimator available. The deviation between the non-instrumented estimator and the IV estimate will give an indication of the effect of using a non-experimental estimator on the parameter estimate.

Another significant deviation from the research design was that the baseline data collection did not take place before the Batch 1 villages started implementing the project. The baseline data collection took place on average 6 months after Batch 1 villages started implementation. Further, the midline data collection took place an average of 9 months after Batch 3 villages started implementation. The delays were a result of the MoNE’s prolonged procurement process to engage the survey fieldwork company and a desire to dispense the funds to the communities. Given these timing issues, in order to assess the impact of the project we will construct measures of dosage, such as months the project was active in a given village.

The consequence of the late baseline survey is that the pre-intervention values cannot be observed from the baseline data for Batch 1 villages. For Batch 3 villages, the intervention had not occurred at the time of the baseline. This is particularly problematic for pre-intervention levels of outcome variables, which in equations (1), (2) and (3) would normally be included in *X*_*ij*0_. With a late baseline, these outcome variables could already have been influenced by the intervention, thus leading to correlation between *X*_*ij*0_ and *T*_*j*_, also in the experimental design.

Our approach to manage this issue is two-fold. For the utilization variables, which we believe responded quickly to the opening of early childhood development services, we intend to reconstruct a variable of utilization before the start of the project based on retrospective data collected in the baseline survey. For child development variables, we intend to use the baseline data to estimate the impact of the intervention after 6 months comparing Batch 1 to Batch 3 villages.

The consequence of the late midline survey is more limited. When conducting the midline analysis in (3), the comparison is no longer between 18 months of implementation and no project, but rather between 20 and 9 months of implementation. This is because project implementation was delayed in Batch 3. By the time the midline data were collected, Batch 3 villages had been implementing the intervention for only 9 months. Therefore, we intend to use the midline data to estimate the impact of the project after Batch 1 villages have received the project for 20 months and Batch 3 villages have received the project for 9 months, that is, the impact of 11 months of differential exposure. For outcome variables which respond quickly to the treatment, such as utilization, this is a problem as both Batch 1 and Batch 3 villages received treatment. Our strategy will be to focus on utilization variables which capture utilization over the entire evaluation period, not only at the time of the survey. For outcome variables which respond more slowly to the treatment, such as child development outcomes, we simply report the comparison as above, indicating that this is the impact of the 18-month difference in treatment duration.

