### Recruitment

The project as a whole covers 50 districts across Indonesia. By the time the MoNE expressed support for a randomized evaluation design, many districts had already decided when each of the 60 project villages would receive funding (that is, districts had already allocated villages to a particular batch), making it too late to implement a randomized roll-out of services in these districts. Districts that had not yet decided when beneficiary villages would receive the project were contacted by the MoNE and asked about their willingness to randomly allocate 20 villages out of 60 to Batches 1 and 3. As batch implementation was to begin 9 months apart, it was anticipated that there would be 18 months between Batches 1 and 3. In deciding upon the final ten districts to participate in the study, the MoNE made an effort to ensure geographic diversity with the goal of producing a sample that broadly represented project districts. These districts were: Sarolangun, Rembang, Gorontalo, Kulon Progo, Sidenreng Rappang (Sidrap), Majalengka, Ketapang, North Bengkulu, Middle Lombok and East Lampung. Random selection at the district level would of course have been preferable and allowed for districts to have been representative of the project, but this was impossible due to timing and lack of willingness of districts to randomize.

Randomization of the 20 villages took place through a public lottery in each district, supervised by MoNE staff. The first ten villages selected were allocated to Batch 1, treatment, and the latter ten were allocated to Batch 3, control (which were to receive treatment 18 months later).

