#### Sampling procedures

The steps taken to obtain the final list of sampled villages are described in the Recruitment section above. The baseline survey contained 310 villages, of which 100 were originally allocated to Batch 1, 20 originally allocated to Batch 2, 100 originally allocated to Batch 3 and 90 allocated to the matched control group. The remainder of this section describes the sampling procedures followed within each village.

In each village, two dusuns were sampled. At baseline it was not clear which dusuns the project would work in and as such the evaluation selected one dusun randomly as well as including the dusun in which the village head’s office was located. The rationale for the selection of the dusun with the village head’s office was that it would have a higher concentration of people and also be a likely location for early childhood services. We felt confident about detecting project participation without yet knowing about project placement as the intervention aimed to have an influence at the village level. On average there are five dusuns per village [28].

Households were randomly selected during the baseline survey from a listing that was created for this evaluation. As individual level enumeration data is not available for Indonesia, the World Bank had to construct a listing. To construct this listing, fieldworkers went to each village, met the village and dusun heads, and asked for a resident roster list of all households by dusun where there was a child aged between 0 and 6 years. In some areas, if the information from the dusun head was incomplete or questionable, this information was cross-checked with records from the posyandu head (integrated child health services clinic) and/or a midwife. In each dusun, survey teams interviewed ten households with children aged 1 and/or 4 years, amounting to 20 households per village and thus 6,200 households in total.

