An estimate of *π* that is not significantly different indicates that the matched control sample would have been a valid control group at midline when using the sample of matched control (*MC* = 1) and randomized control villages (*MC* = 0). If this is true, it also increases the ‘comfort factor’ of making this assumption at endline. If not, it provides an indication of the direction in which the estimates from (1) will be biased.

At midline, the experimental design makes it possible to estimate the average treatment effect of the first 18 months of intervention with minimal assumptions. Batch 3 villages will still be a valid control group. Using data from Batch 1 (*T* = 1) and Batch 3 (*T* = 0), the average treatment effect can be estimated by:

(3)$$Y_{\mathrm{ij}1}=\rho +X_{\mathrm{ij}0}\varphi +\vartheta T_{j}+\epsilon_{\mathrm{ij}}$$

Outcomes will be indicators of child development and utilization of early childhood development services. The latter is of interest as the projects aims to increase child development through improved access to early childhood development services. Considering both types of outcome variables provides an opportunity to evaluate the pathways of impact.

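### After the batch switching, the plan does not commit to reporting the midline comparison by lottery assignment, and the exposure scale for its instrumental-variable estimate is inconsistent

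*Protocol article*

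**What the plan says.** Under Recruitment, villages are assigned by public lottery in each district: "The first ten villages selected were allocated to Batch 1, treatment, and the latter ten were allocated to Batch 3, control". Under Planned analyses, equation (3) compares Batch 1 (T = 1) with Batch 3 (T = 0) at midline, and the article says that "the experimental design makes it possible to estimate the average treatment effect of the first 18 months of intervention with minimal assumptions".

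Under Deviations from planned design and consequences for analysis, the article reports that the assignment was not followed: "This happened in our case for 20 out of 310 villages". It proposes an instrumental-variable (IV) version of equation (3), in which T "is replaced with the actual batch, or the time period of the actual intervention at the time of the survey, and is instrumented with" the original T. It then compares this with a non-instrumented estimate and says that the deviation between the two "will give an indication of the effect of using a non-experimental estimator on the parameter estimate".

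The same section says that midline fell on average 9 months after Batch 3 started. It describes the midline contrast as 20 against 9 months, or 11 months of differential exposure. It closes by saying that, for slowly responding outcomes, the comparison will be reported as the effect of an 18-month difference. The Discussion says around 11 months. The dose measure is described only as something like the months that the project was active in a village.

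**The concern.** The Discussion rests the trial's internal validity on random assignment and attributes midline differences between treatment and randomized control villages to the project alone. That holds for villages compared as drawn. It does not hold for villages compared by the batch they ended up in, because districts moved villages for their own convenience and proximity. The comparison by lottery assignment needs no dose measure and no assumption that assignment acts only through dose, yet neither estimate named after the deviations is that comparison.

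The IV regressor is also left open between actual batch and exposure time. If time is chosen, the reported effect depends on a month count on which the article disagrees with itself. If batch is chosen, a reader still cannot tell whether the effect belongs to 11 or 18 months of extra exposure.

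**Working it through.** **1. Which estimates are named.** With one instrument and the same covariates in both stages,

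IV = ITT / first stage,

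where ITT is the outcome difference by lottery assignment and the first stage is the difference in actual batch (or months) by lottery assignment. If the non-instrumented estimate were the ITT, its ratio to the IV estimate would be the first stage exactly. That ratio reflects compliance only and says nothing about a non-experimental estimator. The stated purpose of the comparison makes sense only if the comparator is the regression on actual batch or time, that is, as-treated. So the two named estimates are IV and as-treated. The later mention of the midline analysis in equation (3) does not say whether batch means assigned or actual.

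**2. The stated exposure contrast.** 20 − 9 = 11 months reproduces. The 18 months at the end of the same discussion does not follow from those figures.

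**3. Check against Table 1.** Midline was July to August 2010, with 1 August as its midpoint.

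| Clock | Window in Table 1 | Months to midline |
|---|---|---|
| Batch 1, grants | Nov to Dec 2008 | 20.0 from mid-window (range 18.0 to 21.9) |
| Batch 3, grants | Nov 2009 to Jun 2010 | 0.0 to 10.0 |
| Batch 3, services | from Jan 2010 | at most 8.0 |

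- Batch 1's 20 months agrees with the grant dates.
- Batch 3's average of 9 months is impossible from service opening, where the maximum is 8.0 (1 January to 31 August 2010).
- From grants, 9 months before 1 August 2010 is 1 November 2009, the first day of the window. An average of 9 therefore needs nearly all grants at the start of a window that runs to June 2010.
- If grants were spread evenly (an assumption), the Batch 3 mean is about 5 months and the contrast about 20 − 5 = 15.
- The abstract starts midline in April 2010. An earlier midline would shorten Batch 3 exposure further, so it does not rescue the 9.

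**4. Effect on a months-scaled IV estimate.** Take an illustrative ITT of 0.20 SD and a compliance factor of 0.8 (step 5):

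- 11 months: 0.20 / (0.8 × 11) = 0.0227 SD per month
- 15 months: 0.20 / (0.8 × 15) = 0.0167
- 18 months: 0.20 / (0.8 × 18) = 0.0139

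The ratios do not depend on the illustrative values: 11/18 = 0.61 (39% lower) and 11/15 = 0.73 (27% lower). The first uses only the article's own two figures. With actual batch as regressor no months enter, so only the label changes.

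**5. Share switched and dilution.** Sampling procedures gives the original allocation as "100 were originally allocated to Batch 1, 20 originally allocated to Batch 2, 100 originally allocated to Batch 3 and 90 allocated to the matched" (the last figure being the comparison villages outside the project). Batches 1 and 3 hold 100 + 100 = 200 villages.

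- Share of all surveyed villages: 20/310 = 6.5%.
- Share of the lottery villages in equation (3): 20/200 = 10%, if all switches lie there.
- If all 20 crossed between Batches 1 and 3, the first stage is 1 − 20/100 = 0.8, however they divide between the arms, and IV = ITT / 0.8 = 1.25 × ITT.
- If all 20 moved to Batch 2 and Batch 2 counts as half-way, the first stage is 1 − (20 × 0.5)/100 = 0.9.

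The direction of the switches cannot be checked because the flow figure is not shown.

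**The case against.** A reader might infer that the ITT effect has been removed from the plan. The documents do not support that. Equation (3) is never withdrawn, the IV estimator is offered in permissive wording, the lottery indicator stays as the instrument, and the ITT is recoverable as IV times first stage. What stands is that reporting it is not committed to.

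A reader might also infer that any IV result moves with the clock. Only the months version does.

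Larger or more precise discrepancies could be drawn from the midpoint of Batch 1's service-opening window in Table 1. That window begins in March 2008, before the Batch 1 grants of November to December 2008 in the same table, so it cannot carry such a figure. The clash between 11 and 18 months needs no midpoint.

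The as-treated regression is presented as a comparison with the IV estimate and not as an effect estimate in its own right; that objection stands.

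Three limits on importance also stand. The main objective is the endline comparison of Batch 1 with matched controls. One district's lottery villages were dropped after randomization for non-compliance. Baseline covariates in equation (3) may already reflect treatment, as the article says. Reporting the lottery comparison cures neither of the last two.

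Ranking ITT against IV could be left to a fuller analysis plan. But the article itself prescribes the replacement of T and itself prints both 11 and 18 months, so these are statements to reconcile and not mere omissions.

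**Conclusion.** The point holds in a limited form. After the switching, the article specifies an IV estimate on an unsettled regressor and an as-treated comparator, and it does not commit to reporting equation (3) on the original lottery assignment. The randomized evidence is not lost, but it is not planned as a reported estimate.

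The exposure scale contradicts itself: 11 against 18 months for one comparison, and a Batch 3 average of 9 months that Table 1 excludes on service opening and makes implausible on grants. A months-scaled effect would be about 39% lower at 18 than at 11 months, with no assumption beyond the article's own figures. The 27% figure at 15 months assumes evenly spread grants. The 10% switched and the 0.8 to 0.9 dilution assume that all 20 switches lie in Batches 1 and 3. This should be corrected before the midline results are reported, but it does not undermine the trial.

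**What to change.** In Deviations from planned design and consequences for analysis:

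- State that equation (3) on the original lottery assignment is reported as the midline ITT estimate, with the IV estimate on actual batch alongside it as secondary.
- Say explicitly that the as-treated regression is a diagnostic only.
- Define once which event starts exposure, reconcile 11, 18 and 9 months with Table 1, and correct the 18-month label.
- Give any per-month scaling as a sensitivity analysis under both the grant and the service-opening clock.
- State the switched share against the 200 lottery villages in Batches 1 and 3, with the direction of the switches.

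The cost is a few sentences and one regression on data already collected. The downside is a smaller midline figure: the ITT would be about 0.8 to 0.9 of the complier effect under the assumption above.

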### Project timetable

The timeline of impact evaluation milestones are presented in Table 1.

**Table 1 T1:** Timeline of impact evaluation milestones

**Impact evaluation milestones**	**Anticipated**	**Actual**
Sample size calculations	December 2006	December 2006
Randomization of 20 villages/districts to T and C status	March to July 2007	March to July 2007
Selection of matched controls	March to July 2007	March to July 2007
Discovery of randomization compliance issues	N/A	December 2008
Batch 1/treatment receives block grants	February 2008	November to December 2008
Batch 1/treatment opens services	December 2008	March 2008 to December 2009
Baseline survey	January 2008	March to June 2009^a^
Batch 3/randomized control receives block grants	May 2009	November 2009 to June 2010
Batch 3/control opens services	July to August 2010	January 2010 to present
Midline survey	March 2010	July to August 2010
Endline survey	Planned for early 2013	February to July 2013

^a^Fieldwork in most districts took place in March and April 2009, with some exceptions. Data collection in Lombok went into June due to some delays in paying enumerators and because the sample was over double that of the other districts. Because it was discovered that data were falsified in Sarolangun and Bengkulu, the World Bank hired a team to re-administer surveys in Bengkulu in June 2009 and in Sarolangun from October to December 2009. *C* control, *T* treatment.

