In addition to external validity, the other caution we have relates to the length of time between when the treatment and randomized control villages received the project. Most research literature to support the benefits of early intervention and child development are long-term studies that in many cases track into adulthood [2,41,42]. The current planned follow-up time for this study is more limited, and showing an impact might be difficult. Initially, the design called for 18 months between baseline and midline as well as 18 months difference in exposure to the project. Due to a combination of lack of adherence to the original study design and planned schedule, the time difference between baseline and midline data collection ended up being around 14 months, while the difference in exposure to the project between Batch 1 and Batch 3 was around 11 months by the time of the midline data collection. This short time span is precisely why the evaluation employed an additional matched control group. The advantage offered by the matched control group is that it allows us to track children who were not exposed to the project for the full 3 years. However, the primary disadvantage with the matched control group is the threat to internal validity.

While the project allowed for the provision of both center-based and outreach services for children, in practice most service provision has been center-based (based on World Bank operational data indicating that only 38% of the centers have organized outreach activities). The block grant was able to be used to equip the centers with toys, learning materials, food supplements and play equipment. The funding was also to be used to hire two local community members associated with each dusun, where one was to be trained as an ECED teacher and the other a community development worker to conduct outreach activities. The community was expected to provide infrastructure for the ECED center. The project funding to communities allows for flexibility in mechanisms of service provision, but stipulates that the services be targeted to children aged 0 through to 6 years with a specific focus on children aged 2 to 4 years, and poor families. This degree of flexibility at a community level means that there may be a large degree of variation across villages, also making it difficult to calculate dose and thus impact.

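### The midline child-development comparison is to be reported as an 18-month exposure difference, although the plan itself gives about 11 months, and the 9-month Batch 3 average behind the 11 fits poorly with Table 1

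*Protocol article*

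**What the plan says.** The section on deviations from the planned design revises the midline analysis in equation (3). It states that "the comparison is no longer between 18 months of implementation and no project, but rather between 20 and 9 months of implementation", and sums this up as "that is, the impact of 11 months of differential exposure". The Discussion repeats the figure ("the difference in exposure to the project between Batch 1 and Batch 3 was around 11 months") and mentions 18 months only as what the design first called for.

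The closing sentence of the deviations section then sets the reporting rule for slowly responding outcomes, with child development as the example: "we simply report the comparison as above, indicating that this is the impact of the 18-month difference in treatment duration".

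The 9 months for Batch 3 comes from the same section: "the midline data collection took place an average of 9 months after Batch 3 villages started implementation". The article does not say whether implementation starts with the grant, with the opening of services, or with something else.

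Table 1 (Project timetable, actual dates) places Batch 1 grants in November to December 2008, Batch 3 grants in "November 2009 to June 2010", Batch 3 service opening in "January 2010 to present", and the midline survey in July to August 2010.

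**The concern.** One contrast carries two durations in one paragraph. The sentence that governs what will be published uses the planned duration, not the one the authors say occurred. Equation (3) at midline is the main randomised comparison, and child development is what the evaluation was set up to measure. A null or small effect reads differently after an 18-month difference in exposure than after 11, and so does any comparison with the 3-year endline result.

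The second layer is whether 11 is itself the right replacement. It rests on a Batch 3 average of 9 months, and the article's own timetable leaves little room for an average that high.

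**Working it through.** **1. The plan's own figure.** Batch 1 had on average 6 months of implementation at baseline (deviations section), and baseline to midline was around 14 months (Discussion): 6 + 14 = 20. Batch 3 had 9. Then 20 − 9 = 11, so the stated 11 is reproduced.

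**2. The label against that figure.** 18/11 = 1.64, an overstatement of 64%, taking the stated 20 and 9 as correct.

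**3. Which clock gives 20 for Batch 1?** From grants in November–December 2008 to midline in July–August 2010 is 19 to 21 calendar months, centred on 20. The stated 20 therefore fits counting from the grant. This is an inference; the article does not say so.

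**4. Batch 3 on the grant clock** (grants November 2009 to June 2010):

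| Survey date | Shortest | Longest | Mean if evenly spread |
|---|---|---|---|
| July 2010 (calendar months) | 1 | 8 | 4.5 |
| August 2010 (calendar months) | 2 | 9 | 5.5 |

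By exact days the extremes are about 0 (30 June to 1 July 2010) and 9.95 months (1 November 2009 to 31 August 2010). With fieldwork centred on 1 August 2010, a mean of 9 needs a mean start of about 31 October 2009, before the first grant month. Even if every interview fell on 31 August, the mean start would have to be about 30 November 2009, although grants ran on to June 2010.

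**5. Batch 3 on the service-opening clock** (January 2010 onward). The longest possible exposure is 1 January to 31 August 2010 = 7.95 months. An average of 9 cannot occur on this clock.

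**6. Contrast on the grant clock.** Calendar-month gaps between Batch 1 and Batch 3 grants:

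- smallest: December 2008 to November 2009 = 11
- largest: November 2008 to June 2010 = 19
- midpoint, and mean under even spread: 15

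By exact days the limits are 10.0 and 19.9. The stated 11 is thus at the low end of the range. Against 15, the 18-month label would overstate by 18/15 − 1 = 20%.

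I give no contrast on the service clock, because Table 1 dates Batch 1 service opening from March 2008, before the Batch 1 grants.

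**7. Midline dates.** The Abstract gives April to August 2010, while the quality-control section and Table 1 give July to August. An April start would shorten Batch 3 exposure further.

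**The case against.** The best defence is that the disputed sentence is a slip that a careful reader would correct. It says the comparison is reported as set out above, which is 20 versus 9, and the correct arithmetic stands a few lines earlier. No estimator, covariate or test changes. This is fair as to the likely cause. The sentence is nevertheless the operative reporting rule, and following it would put the wrong duration on the result.

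The defence is stronger on Table 1. The table gives only ranges, the even spread is an assumption, and the start of implementation is undefined. A reader might infer that Table 1 rules out a 9-month average on every clock. It does so only from service opening. On the grant clock the ceiling is 9.95 months, so 9 is implausible but possible, and a start before the grant is conceivable. The 64% also takes 11 as correct; if the true contrast is nearer 15, the error is smaller, and 18 itself lies within the grant-clock range.

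Three further readings are tempting but unsupported:

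- **That this is the only randomised estimate.** The plan also compares Batch 1 with Batch 3 on the baseline data, after 6 months.
- **That readers would be told Batch 3 had no project.** Planned analyses does say "Batch 3 villages will still be a valid control group", but that describes the intended design. The deviations section states that both batches had received treatment by midline.
- **That the label enters the dose or instrumental-variable models.** Those use months active in the village, or the actual batch or intervention period. The 18 is not an input, and no per-month rescaling by it is planned.

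**Conclusion.** The reporting rule is wrong as written. It states 18 months for a contrast that the same paragraph and the Discussion put at about 11, an overstatement of 64% on the plan's stated inputs. This part needs no assumption beyond those inputs.

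The 9-month Batch 3 average is doubtful but not disproved: near the ceiling when counted from the grant, and out of reach when counted from service opening. On grant dates the true contrast could be about 11 to 19 months. The midpoint of 15 holds only under even spread. Neither 18 nor 11 should therefore be adopted without checking village dates. The fault lies in how the exposure contrast is stated and defined; it does not invalidate equation (3) as a comparison of the assigned batches.

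**What to change.** - Remove the 18-month label from the closing sentence of the deviations section.
- Define when exposure starts (grant or service opening).
- From village dates, compute months of exposure at midline by assigned batch, and give the mean difference between Batch 1 and Batch 3 with its spread.
- Report that figure as the exposure contrast for equation (3), and use the same clock in the dosage measures already planned.
- Reconcile the 9-, 11- and 20-month statements in the deviations section and the Discussion with Table 1, correcting or explaining the 9-month average.

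The cost is a few sentences and one tabulation. The dosage measures already planned need months of project activity by village, so little extra data work should be involved. No new data collection or change of estimator follows.
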